### Inclusion criteria

18 years or older and of Aboriginal and/or Torres Strait Islander descent.Able to provide written informed consent.English-language proficiency sufficient to complete study questionnaires.A current (30-day) diagnosis of depression (any subtype), with or without other mood, anxiety or substance use disorders as diagnosed from a Structured Clinical Interview for DSM-5 Disorders (SCID-5)^23^ interview.

### Exclusion criteria

Cognitive impairment, as determined through the Kimberley Indigenous Cognitive Assessment (KICA) screening.^24^High-risk of suicide, as determined by the SCID-5 clinical interview, and question nine on the BDI.^25^Recent (past 6 weeks) change in psychiatric medication.Any mental or physical condition requiring hospital admission.Diagnosis of organic brain disorder.Bipolar disorder.Psychotic disorder.Another mental disorder (for example likely personality disorder based on client self-report) that, in the opinion of a clinical psychologist, is likely to interfere with their ability to engage in or complete the study.Another medical condition likely to prevent participation in the study for 12 months.

### Participant recruitment procedure

Participants will be individuals attending participating AMSs and mainstream medical services in either Toowoomba or Warwick. Recruitment methods will include: advertising using flyers and posters, recruitment in the AMS waiting rooms and word of mouth. If individuals are interested, they will be provided a reply slip to fill out, via mail or in person, and will be given a participant information pack. An appointment for the screening interview may be made at this time if they are agreeable or will be made based on the suggested time that the participant indicates on the reply slip. The researchers will meet with the staff member/s prior to recruitment and ensure they understand the RCT sufficiently to provide the initial introduction to potential participants at the recruitment stage.
Advertising: posters advertising the project will be displayed in the participating AMSs and medical services, and on local community noticeboards.Cold calling: a dedicated and trained staff member of the AMS will contact participants from our previous studies who consented to be re-contacted for future research to discuss the study. Those interested in finding out more will be posted a participant information pack.Waiting room recruitment: a trained staff member will recruit participants from the waiting area of the AMS or medical service. The staff will approach potential participants and provide information about the study.Word of mouth: past studies with this population have shown word of mouth to be an effective method of recruitment so this will be used for the current study.

### Study arms

#### Intervention – IMMHC

This will be documented and delivered by qualified psychologists trained in the treatment package. The psychologists will receive weekly cultural and clinical supervision and fidelity will be assessed by video-taping a random selection of sessions (*n* = 20) over the duration of the intervention. These tasks will be performed by the supervising clinical psychologist. Competence and fidelity to CBT will be assessed using the Cognitive Therapy Scale – Revised to rate a random selection of videotaped sessions (*n* = 20) over the duration of the entire study. Treatment will consist of both individual and group psychotherapy, as described below. Individual sessions will comprise tailored CBT and traditional spiritual healing; group sessions (co-facilitated with an indigenous health worker) will focus on skills practice, including yarning (informal conversation) about successes and difficulties in application, and developing peer support and reinforcement in this area.
Individual treatment. The first session will involve the assessment of cognitive and behavioural factors maintaining the disorder. As our previous study^2^ demonstrated that these assessments are typically lengthy, the sessions will be up to 90 min. The treating psychologist will then develop a tailored 6-month treatment plan, in consultation with a senior clinical psychologist and the traditional healer, as well as the participant. Changes in symptomatology may warrant adjustments or changes to the treatment plan. A minimum of 10 and up to 12 sessions of individual treatments will be provided by qualified psychologists using a combination of face-to-face delivery for primary treatment and telephone delivery to facilitate skills practice. The duration of this intervention period will vary for participants, based on their tailored 6-month treatment plan.Group treatment. The efficacy of CBT relies on the use of ‘homework’ or skills practice by the patient to maintain treatment effects. Based on our previous research, we believe that skills practice is likely to be difficult for many Indigenous participants, so we will use traditional healing sessions as a way to do homework. Traditional healers will work with participants to find out what their homework is and practise this with individuals. In addition, follow-up calls by the traditional healers and project team to check on participants and support them between sessions will be incorporated. Group treatment will also be provided via a ‘yarning skills group’ as an adjunct to individual sessions. The purpose of this group is to build on skills learned in individual sessions, provide further peer support in a positive supportive environment, and focus on personal and group strengths. Group treatment aims to be therapeutic, strengths-based, and culturally friendly by: using traditional and spiritual healers, psychologists and Indigenous care co-coordinators as group facilitators; exploring successes in applying skills and learnings obtained from individual sessions; and allowing peers to support each other through learning new behaviours. Consistent with another evidence-based therapy that has adapted CBT for complex presentations using both individual and group CBT; a different psychologist will be used for individual and group sessions. Participants will be offered three to five group sessions over a period of 6 months, with no more than ten participants in each session group.

#### TAU

All diagnoses arising from the SCID–5 Screening interview will be entered on patient files and clients’ name provided to the AMS or medical service for follow-up. Participants who are randomised into the TAU group will receive the standard treatment offered to clients with a diagnosed mental illness. This will include a first appointment with a general practitioner who will then determine the most appropriate treatment required for the participants. This may include referral to a psychologist; a mental healthcare plan; and/or medication.

#### Post-study treatment for the control group

Should the IMMHC prove more efficacious than TAU, participating AMSs and/or medical services will adopt it as a standard treatment option for individuals diagnosed with depression. Following the intervention study, the 6-month IMMHC intervention will also be made available to research participants in the control group. It is the intention of the research team to use psychologists participating in the study where practicable, including the delivery of the IMMHC. This should ensure that at least one IMMHC trained psychologist is available at the participating AMS/medical service to deliver the model of care post-study. In addition, should the IMMHC prove more efficacious than TAU, the research team undertakes to provide a post-study training module to ensure that there are staff adequately qualified to deliver the IMMHC package into the future.

#### Interviews

All participants, from both the intervention and TAU groups, will be invited to attend individual and/or group interviews at the conclusion of the trial, after the follow-up assessments post-intervention have been completed, to discuss the reasons why participants may or may not engage with the study or choose to drop-out. Interviews will be audio-recorded for subsequent qualitative analyses.

### Outcome measures

#### Primary outcome measure

The difference between changes in the TAU and IMMHC groups on depression scores as measured by the BDI-II from baseline to 6 months.

#### Secondary outcome measures

The difference in change of scores as measured by BDI-II from baseline to 12 months, between the TAU and IMMHC group.Comparison of changes in quality of life measured using the Assessment of Quality of Life (AQoL)-8D.^26^
Changes in quality of life between baseline and 6 months; other changes between baseline and 12 months.Other changes in mental health.
Anxiety: changes in Beck Anxiety Index (BAI^27^) – baseline to 6 months and baseline to 12 months.Substance use: changes in scores based on the Alcohol, Smoking and Substance Involvement Screening Test (ASSIST).^28^Changes in the presence of major depression, anxiety or substance use disorder(s), as established by a SCID-5-Clinician Version (SCID-5-CV) interview at 12 months.Changes in number of mental health diagnoses and patterns of psychotropic medication use.
Diagnostic status of initial mental health conditions will be evaluated using SCID-5-CV at 6 months and 12 months.Medications (class, dosage and frequency) will be captured for both the groups and compared.Thematic analysis to explore reasons why participants may or may not engage with the study or choose to drop-out.

### Data analysis

Data will be gathered at the point of initial screening for eligibility, baseline, 6- and 12-month post baseline follow-ups, and at the focus groups and interviews. See the schedule of assessments in Appendix 1.

#### Quantitative analysis

Intention-to-treat principles will be used for all analyses. Differences in mean change in BDI-II scores from baseline to 6 months between the two groups will be analysed using repeated measures ANOVA, with treatment as the between-subjects factor, and time as within-subjects factor, and an interaction term (time and treatment group). Additional analyses will use mixed models adjusting for baseline covariates including quality of life. We will also calculate the differences between the groups using hierarchical mixed models for continuous variables (BDI-II and BAI scores measured at three time points – baseline, 6 months post-intervention and 12 months post-intervention) containing random intercept and random slope as well as fixed effects for treatment. We will also evaluate changes in diagnostic status using logistic and/or Poisson regression models.

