### Sample size calculation

The sample size estimates are based on a 2 × 2 repeated measures design comparing changes in BDI-II scores between the two groups (IMMHC and TAU). The primary goal of the study is to compare the change across time in the IMMHC group with the change across time in the TAU group. Sample sizes of 44 in both groups achieve 80% power to detect a difference in mean changes of 6.8 with a standard deviation of 12.8 at the first time point, a standard deviation of 12.0 at the second time point, and a correlation between measurement pairs of 0.6. The significance level (alpha) is a *P*-value of 0.05 using a two-sided, two-sample *t*-test. Based on previous research and experience a 20% drop-out rate is anticipated. Assuming a 20% drop-out rate, the total sample size required is 110.

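### The named primary ANOVA leaves out anyone without a 6-month BDI-II score unless values are imputed, so it does not by itself deliver the stated intention-to-treat analysis

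*Protocol article*

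**What the plan says.** The primary outcome (Primary outcome measure) is "The difference between changes in the TAU and IMMHC groups on depression scores as measured by the BDI-II from baseline to 6 months".

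The Quantitative analysis section opens with a general rule: "Intention-to-treat principles will be used for all analyses". Its next sentence fixes the primary method. Mean BDI-II change from baseline to 6 months "will be analysed using repeated measures ANOVA, with treatment as the between-subjects factor, and time as within-subjects factor", plus the interaction of the two.

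Two kinds of mixed model follow. The first is introduced as supplementary: "Additional analyses will use mixed models adjusting for baseline covariates including quality of life". The second covers BDI-II and the anxiety score at baseline, 6 and 12 months, with random intercept and slope: "We will also calculate the differences between the groups using hierarchical mixed models for continuous variables".

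The Sample size calculation section says: "Sample sizes of 44 in both groups achieve 80% power to detect a difference in mean changes of 6.8". It then allows for loss: "Assuming a 20% drop-out rate, the total sample size required is 110".

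The article does not say how a missing BDI-II score is handled. It does not restrict any analysis to completers, and it neither provides for imputation nor rules it out.

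**The concern.** The article does not leave the primary method to a later document. It names one, and that method needs both scores from each participant. On the usual reading of intention-to-treat, in which all randomised participants count, the general rule and the named method do not fit together without a further step that the article does not give.

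The one confirmatory comparison is at stake. The arms ask very different things of participants. IMMHC offers 10 to 12 individual sessions and three to five group sessions over about 6 months, while TAU starts with a general practitioner appointment and varies from there. It is plausible that the people who leave differ in severity between the arms. A change-score comparison among those who stay would then mix the treatment effect with selection. The article expects disengagement to matter, since it plans interviews on why participants drop out.

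**Working it through.** **Inputs.** All are from Sample size calculation: SD 12.8 at the first time point and 12.0 at the second, correlation 0.6, difference in mean change 6.8, two-sided alpha 0.05, 44 per group, 20% drop-out, total 110.

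**Step 1. Reproduce the plan's figures.**
- SD of change = sqrt(12.8² + 12.0² − 2 × 0.6 × 12.8 × 12.0) = 11.11.
- Noncentral t power for 6.8 is 80.1% at 43 per group and 81.0% at 44, so 44 per group for 80% power is sound.
- 88 / (1 − 0.20) = 110. The total is correct.

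**Step 2. What the named test uses.** With two time points, the treatment-by-time F statistic is the square of the two-sample t statistic on change scores. A numerical check on a simulated data set of 44 per group gave 7.034 for both. Someone with no 6-month score has no change score and drops out of the test unless a value is imputed. At 20% drop-out that is 0.20 × 110 = 22 people, leaving 88.

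**Step 3. When the completer estimate goes wrong.** Let z be the standardised baseline score. Given z, expected change moves by (0.6 × 12.0 − 12.8)z = −5.6z. Assume drop-out of 20% per arm, with log-odds rising by 0.7 per baseline SD (odds roughly doubling). Mean z among those retained is then −0.130, so mean change among completers in that arm shifts by 5.6 × 0.130 = 0.73 points toward less improvement. A slope of −0.7 gives the same shift in the other direction. The slopes are assumptions, because the article gives no drop-out mechanism.

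| Assumed drop-out | Completer estimate (true 6.8) | Estimate conditioning on baseline |
|---|---|---|
| Random in both arms | 6.8 | 6.8 |
| +0.7 in both arms | 6.8 | 6.8 |
| IMMHC +0.7, TAU 0 | 6.8 − 0.73 = 6.1 | 6.8 |
| IMMHC +0.7, TAU −0.7 | 6.8 − 1.46 = 5.3 | 6.8 |
| IMMHC −0.7, TAU 0 | 6.8 + 0.73 = 7.5 | 6.8 |

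Simulation gave the same results to within about 0.1. With 44 per group and SD 11.11, power is 81% at 6.8, about 72% at 6.1 and about 60% at 5.3.

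**Step 4. When the alternative also goes wrong.** Suppose IMMHC drop-out depends instead on the unseen 6-month score, with the same slope. Among those retained, the 6-month mean falls by 12.0 × 0.130 = 1.56 and the baseline mean by 0.6 × 12.8 × 0.130 = 1.00.
- Completer estimate: 6.8 + 1.56 − 1.00 = 7.4.
- Baseline-conditioned estimate, with regression slope 0.6 × 12.0 / 12.8 = 0.56: 6.8 + 1.56 − 0.56 × 1.00 = 7.8.

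Here the model that conditions on baseline is further from the truth.

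**The case against.** The strongest defence is that the conflict depends on something unstated. Intention-to-treat can mean only that people are analysed in the arm to which they were randomised, and the ANOVA satisfies that. It can also be run on imputed data. Missing-data rules are commonly left to an analysis plan or full protocol, neither of which is shown. This stands: the absence of an imputation rule is no finding, and nothing shows that the rule cannot be met. What remains is that the article itself fixes a primary method that needs such a rule, and ranks below it the models that need none.

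A reader might infer more, and the documents do not support it:

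- **That a completer analysis is intended.** No sentence says so. Dividing by one minus the drop-out rate is routine allowance for lost information whichever analysis follows, so 88 and 110 say nothing about the analysis set.
- **That drop-outs' baseline scores and later 12-month scores are thrown away.** They fall outside the primary test, but the planned three-time-point mixed model can use them.
- **That any link between drop-out and severity biases the result.** It does not. An equal link to baseline severity in both arms leaves the estimate at 6.8.
- **That the effect will be underestimated.** The direction is open. The same assumed slope with its sign reversed overstates the effect.

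**Conclusion.** The point holds in a limited form. Unless imputation is specified, the named primary test leaves out participants without a 6-month BDI-II, about 22 of 110 at the plan's own drop-out rate. It therefore does not by itself give an intention-to-treat analysis of everyone randomised. Bias is possible but not shown. It requires drop-out to relate to severity differently in the two arms, or to depend on the unseen outcome. Under the assumed baseline slopes it runs from about a fifth too small (5.3) to about a tenth too large (7.5), against 6.8. The article gives nothing from which to judge which mechanism is likely, so these figures show sensitivity and are not forecasts. The sample size stands. This is a cheap improvement to the confirmatory analysis, not a flaw that invalidates the design.

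**What to change.** Make the primary analysis a likelihood-based mixed model on all randomised participants, using BDI-II at baseline, 6 and 12 months. Specify categorical time, a treatment-by-time term, unstructured covariance and a common baseline mean across arms, and name the 6-month treatment contrast as the primary test. Keep the repeated measures ANOVA, labelled as a completers-only sensitivity analysis. Add a delta-adjusted sensitivity analysis for participants without a 6-month score, because the mixed model relies on missing at random and can be the more biased of the two when drop-out depends on the unobserved 6-month score. If the ANOVA is to remain primary, stating an imputation rule for missing 6-month scores would also reconcile it with the intention-to-treat sentence.

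The cost is wording and some extra analysis work. All three BDI-II assessments are already in the schedule of study assessments, and mixed models are already planned. No change to 110 is needed. A common baseline mean makes the 6-month contrast behave like a baseline-adjusted comparison, with residual SD 12.0 × sqrt(1 − 0.6²) = 9.6 against 11.11 for the change score, so precision should not suffer under the plan's own assumptions.

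### The primary analysis tests raw BDI-II change; it is valid and meets its power target, but adjusting for baseline BDI-II would cut the variance by 25% on the plan's own figures

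*Protocol article*

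**What the plan says.** The protocol article (Primary outcome measure) defines the outcome as the between-group difference in BDI-II change from baseline to 6 months. Under Quantitative analysis the test is named: "Differences in mean change in BDI-II scores from baseline to 6 months between the two groups will be analysed using repeated measures ANOVA". Its terms are group (between subjects), time (within subjects) and the interaction of the two.

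The Sample size calculation uses a matching test, a two-sample t-test on mean changes. Its claim is this: "Sample sizes of 44 in both groups achieve 80% power". The target is a 6.8-point difference between the arms' mean changes. The assumed SDs are 12.8 at baseline and 12.0 at 6 months, and the two scores are linked by "a correlation between measurement pairs of 0.6". Attrition is then allowed for: "Assuming a 20% drop-out rate, the total sample size required is 110".

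Two further sets of models follow under Quantitative analysis. One is a set of additional mixed models with baseline covariates, of which quality of life is given as an example. The other is a set of hierarchical mixed models over three time points for BDI-II and BAI. Neither is presented as the primary test, and neither is said to adjust for baseline BDI-II.

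**The concern.** With one baseline and one follow-up measurement, the time-by-treatment term of a repeated measures ANOVA is algebraically the two-sample t-test on change scores. That test subtracts the whole baseline score from the 6-month score, which fixes the baseline slope at 1. When baseline and follow-up correlate at 0.6 with similar standard deviations, the best slope is well below 1.

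Two things follow:
- The estimate has a larger variance than one adjusted for baseline, so the same participants give less power.
- If the arms differ by chance at baseline, the change score removes more of that difference than it should. The Randomisation procedure describes blocking but mentions no stratification by baseline severity, so the described design does not limit such imbalance.

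At stake is precision in a trial that expects 44 analysed participants per arm and has about 81% power at the assumed correlation.

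**Working it through.** **Inputs** (all from Sample size calculation): baseline SD 12.8; 6-month SD 12.0; correlation r = 0.6; difference 6.8; two-sided alpha 0.05; 44 per arm analysed; 20% drop-out. It is assumed that the SDs and the correlation are the same in both arms.

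**1. Reproduce the plan's figure.**
- Var(change) = 12.8² + 12.0² − 2 × 0.6 × 12.8 × 12.0 = 163.84 + 144 − 184.32 = 123.52, so SD = 11.11.
- SE of the difference at 44 per arm = 11.11 × √(2/44) = 2.37. The noncentrality is 6.8/2.37 = 2.87.
- Noncentral-t power with 86 df is 81.0%. The smallest n for 80% is 43 per arm, so the stated 44 is sound.
- 88/(1 − 0.20) = 110, as stated.

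**2. Adjust for baseline BDI-II.**
- Best slope = r × SD₂/SD₁ = 0.6 × 12.0/12.8 = 0.56. The change score uses 1.
- Residual variance = SD₂² × (1 − r²) = 144 × 0.64 = 92.16, so SD = 9.60.
- Ratio = 92.16/123.52 = 0.746, a reduction of 25.4%.
- SE at 44 per arm = 9.60 × √(2/44) = 2.05. The noncentrality is 6.8/2.05 = 3.32.
- Noncentral-t power with one further df lost is 90.7%. It is 90.4% if the variance is inflated by 1 + 1/84 for estimating the slope.
- Difference detectable with 80% power at 44 per arm: 6.71 points as planned, 5.80 adjusted.
- About 33 per arm with adjustment would give the 80% power that the planned test needs 43 per arm to reach.

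**3. Chance imbalance.** The SE of the baseline difference at 44 per arm is 12.8 × √(2/44) = 2.73 points. Using slope 1 in place of 0.56 shifts the estimate by (1 − 0.5625) × 2.73 = 1.19 points for a one-SE imbalance. That is 1.19/6.8, or about 18% of the target difference. If the arm with more severe depression at baseline is IMMHC, the shift favours IMMHC; if it is TAU, the shift favours TAU. Over repeated randomisations the shift averages to zero.

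**4. Dependence on the correlation** (SDs held, 44 per arm, difference 6.8).

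| r | Var, change | Var, adjusted | Reduction | Power, change | Power, adjusted |
|---|---|---|---|---|---|
| 0.5 | 154.2 | 108.0 | 30% | 72% | 86% |
| 0.6 | 123.5 | 92.2 | 25% | 81% | 91% |
| 0.7 | 92.8 | 73.4 | 21% | 91% | 96% |
| 0.8 | 62.1 | 51.8 | 16% | 98% | 99% |

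**The case against.** The plan is coherent. The objective, the primary outcome, the sample size and the named test all concern the same difference in change. The 44 per arm and the total of 110 are right for that test. Under randomisation the test is unbiased and keeps its alpha. All of this stands, and it makes the point one of efficiency only.

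A reader might infer from the variance figures that the trial is underpowered or its result biased. The documents do not support that: at the stated inputs the planned test reaches 81%. A reader might also infer that a change score leaves baseline imbalance partly uncorrected. The reverse is true, because a slope of 1 exceeds 0.56. Under-correction would describe a comparison of raw 6-month scores, which is not planned.

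The covariate list for the additional mixed models is open, since quality of life is only an example, so one cannot say that baseline BDI-II is excluded from every analysis. A fuller analysis plan may also specify more. But these models are additional, and the article does name the primary method, so they do not make the primary test efficient.

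Finally, the article gives no source for r = 0.6. At 0.7 or 0.8 the planned test already has 91% or 98% power, and the gain is small.

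**Conclusion.** The point holds as a loss of efficiency, not a flaw in validity. At the plan's own inputs, adjusting for baseline BDI-II lowers the variance by 25%. It raises power for 6.8 points from 81% to about 90–91% and lowers the detectable difference from 6.7 to 5.8 points. About a quarter is the loss at r = 0.6 only; over r = 0.5 to 0.8 it runs from 30% down to 16%. The direction is the same throughout that range, and the benefit matters most if the correlation is lower than assumed: at r = 0.5 the planned test drops to 72% power while the adjusted test keeps about 86%. The figures assume equal SDs and correlation in the two arms, a linear relation between baseline and 6-month scores, and 44 analysed per arm. The change is well worth making, but the trial does not depend on it to meet its stated power.

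**What to change.** State the primary analysis as the between-group difference in 6-month BDI-II adjusted for baseline BDI-II. Use either ANCOVA or a mixed model that constrains the two arms to a common baseline mean. With baseline in the model, taking change or the 6-month score as the response gives the same treatment coefficient, so the primary outcome can stay as worded. Report the unadjusted change comparison as supportive, and name baseline BDI-II explicitly among the covariates of the additional models.

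Keep 110 participants and treat the gain as a margin against a lower correlation or higher drop-out than assumed. The sample size text needs only a sentence saying that it is conservative for the adjusted analysis. The schedule of assessments already includes BDI-II at baseline and 6 months, so the cost is a change of wording, to be made before any outcome data are seen by arm.
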